**Figure 1 figure1:**
[figure not shown]
Flowchart of the bar code-assisted medication administration (BCMA) process in hospitals.

**Table 2 table2:** Classification of workarounds in the bar code-assisted medication administration process^a^.

Workaround type	Example workaround
Procedure related: standard operating procedure, or procedure unclear or unknown	Nothing scanned
Patient related: no patient wristband or patient not in the room	Bed scanned, or loose wristband scanned, patient unscanned
Medication related: medication not bar coded	Unscanned, unidentified medication given
Nurse related: nurse disturbed	Nurse forgets patient or gives medication twice
Computer or scanner related: computer or scanner down or broken	Signals or alerts unseen, unscanned medication given
Other workarounds	Medication scanned for multiple patients; half tablets scanned as full dose

^a^Derived from Koppel et al [26].

**Table 3 table3:** The most basic characterization of medication administration errors (MAEs)^a^.

MAE type	Example MAE
Omission	Drug prescribed, but not administered
Unordered drug administration	Drug administered, but not prescribed
Wrong dosage form	Drug dosage form administered to the patient deviating from prescribed dosage form: solution as an alternative to tablet
Wrong route of administration	Drug given by a wrong route of administration: oral liquid administered intravenously
Wrong administration technique	Drug administered using a wrong technique: intravenous push instead of intravenous infusion
Wrong dosage	Drug dosage too high or low: 20 mg instead of 20 μg
Wrong time of administration	Drug given at least 60 minutes too early or too late

^a^From van den Bemt et al [42].

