### Data Collection

We will use disguised observation [30-34] to collect data. A total of 3 trained observers (undergraduate students, writing their master’s thesis) from the School of Pharmacy, University of Groningen and Utrecht University, the Netherlands, will observe the nurses while they give drugs to inpatients. To prevent nurses adjusting their behavior in the BCMA process while under observation, the observer will be introduced as being on the ward to monitor the performance of the medication distribution system on that ward. The observer will take part in several planned medication administration rounds on that ward and also observe unscheduled medication administrations. The observer will randomly pick a medication administration round with a minimum of 3 rounds every day and a weekly minimum of 18 rounds. During the different rounds, the observer will observe as many different nurses as possible. To prepare for the observation, the observer will study the standard operating procedures or the applicable drug administration procedures of the specific ward and the agreements on the BCMA process of that ward. In practice, the observer will accompany the nurse who administers the medication using the BCMA system and observe the administration of each dose of medication to the patient. The observer will record the nurses’ actions of giving drugs to the patients (according to the forms in Multimedia Appendix 1,Multimedia Appendix 2, and Multimedia Appendix 3). After each observed medication administration round, we will collect a (printed) computer output of the medication for that specific patient, day, and round from the hospital’s electronic patient records. Consequently, we will compare observation records with the prescribed medication on this computer output and with available standard operating procedures of the BCMA process for that specific ward, to identify workarounds and MAEs. We designed an Access database in which we will record the observation data and which we will link to each patient’s prescription and medication data.

If the observer becomes aware of a potentially serious error, the observer will intervene for ethical reasons, but the data will be included in the study.

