### Definitions and Classification

Workarounds are defined as “informal temporary practices for handling exceptions to normal workflow” for that specific ward and are operationalized as deviations from the available protocols [24]. Figure 1 depicts the BCMA workflow and the potential risk factors for workarounds in the BCMA process. We will classify workarounds using a self-developed classification system (Table 2) derived from the system of Koppel et al [26]. Workarounds can be related to patient identification, the scanning process, the alert signals, and other procedures, or can be work related. Allan and Barker [41] defined MAEs as “the administration of a dose of medication that deviates from the prescription as written (or ordered by CPOE) on the patient medication chart, or from standard hospital policy and procedures.” We will compare drug administrations with the doctor’s prescriptions as noted in the CPOE system in the pharmacy database. We will exclude intravenous and nonintravenous preparation errors because these errors are not preventable by BCMA and are thus unlikely to be influenced by workarounds in the BCMA process. We will classify the MAEs using the classification of van den Bemt et al [42] (Table 3). We will divide the number of erroneous medication administrations (containing 1 or more errors) by the number of observed drug administrations plus the number of omissions, thus using the concept of opportunities for errors as in other MAE research [43].

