### Statistical Analysis

Data will be analyzed using IBM SPSS Statistics version 22 (IBM Corporation). We will analyze the potential association between workarounds and the occurrence of MAEs using univariate multilevel logistic regression, with the proportion of medication administrations with 1 or more errors as the dependent variable and the occurrence of workarounds as the independent variable. The nurse and the patient will be the levels in the multilevel analysis. We will analyze the occurrence of workarounds as a categorical variable, with the following categories: no workarounds (reference category), 1 workaround, 2 workarounds, and 3 or more workarounds. We will adjust for potential confounders by using multivariate multilevel logistic regression. The parameters in the multivariate multilevel logistic regression model will be hospital, ward type, day of the week, time schedule of medication administration rounds, ATC code, the number of drugs per patient per round, and the route of administration. We will report the adjusted odds ratio and 95% confidence interval. For the frequency and type of workarounds and MAEs, we will use descriptive statistics. Univariate and multivariate logistic regression will determine the association of the risk factors with the workarounds.

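### Table 2 lists events as workarounds that Table 3 counts as MAEs, so one event can set both exposure and outcome in the primary model

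*Protocol article*

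**What the plan says.** In the Protocol article, Methods, Definitions and Classification, a workaround is an informal, short-term way of coping with an exception in the ward's workflow, "operationalized as deviations from the available protocols". Workarounds are classified with Table 2. Its nurse-related row (nurse disturbed) has one example entry: "Nurse forgets patient or gives medication twice".

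The same section takes its MAE definition from a cited source: a dose that departs from the prescription "or from standard hospital policy and procedures". It then says that administrations are compared with the prescriptions in the CPOE system and that errors are classified with Table 3. Table 3 describes an omission as "Drug prescribed, but not administered" and a wrong dosage as "Drug dosage too high or low". It also has a category for drugs given without a prescription. Omissions are added to the denominator. The one stated exclusion from the outcome is "We will exclude intravenous and nonintravenous preparation errors".

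Under Data Collection, the observation records are compared with the prescriptions and with the ward procedures "to identify workarounds and MAEs". Under Statistical Analysis, the primary model, a logistic regression that has nurse and patient levels, is set up "with the proportion of medication administrations with 1 or more errors as the dependent variable and the occurrence of workarounds as the independent variable", and exposure is grouped as none, one, two, or three or more workarounds.

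**The concern.** An association between exposure and outcome is informative only if each can occur without the other. The nurse-related example in Table 2 describes what happened to the dose: it was missed, or it was given again. Table 3 records the same facts as errors. A dose coded this way is exposed and a case because of how the event is named, whatever bypassing the bar code check does.

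Such rows move the odds ratio in one direction, upward. Masked or perfectly reliable coding would not remove them, because the fault is in the definitions. Adjustment for hospital, ward type, ATC code or route would not remove them either. At stake is the main conclusion: the study could report that workarounds go with errors partly because some errors were counted as workarounds.

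**Working it through.** **Comparison of the tables.** No figure in the article needs to be reproduced here, because the point rests on definitions.

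- Patient forgotten: a nurse-related workaround in Table 2, an omission in Table 3.
- Drug given twice: a nurse-related workaround in Table 2, a wrong dosage or unordered drug in Table 3.
- Nothing scanned, bed scanned, half tablet scanned as a full dose: workarounds in Table 2, but not in themselves errors of any Table 3 type.

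The overlap is therefore firm for the nurse-related row and is not shown for the other rows. Neither event in that row is a practice adopted to handle an exception, so the row also conflicts with the article's workaround definition. Because omissions enter the denominator, whether a forgotten dose is an exposed case or an unexposed case depends on how that row is coded.

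**Inputs for scale.** From the article: 6000 doses (Abstract), 8% with a workaround and a planned relative risk of 2 (Sample Size Calculation). Exposed doses: 0.08 × 6000 = 480; unexposed: 5520. Assumed: true relative risk 1; p0, the MAE rate without a workaround; and f, the share of workaround doses that are MAEs by definition. The article gives neither p0 nor f. It gives an overall error rate of about 10%, which it says includes errors caused by workarounds. I therefore use p0 = 10% and two alternatives: 9.26%, from 10% / (0.92 + 0.08 × 2), and 5%.

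**Formulas.** The rate in exposed doses is p1 = f + (1 − f) × p0. Then RR = p1/p0 and OR = [p1/(1 − p1)] / [p0/(1 − p0)].

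Example, p0 = 0.10 and f = 0.05 (24 of 480 doses): p1 = 0.05 + 0.95 × 0.10 = 0.145, RR = 1.45, OR = (0.145/0.855)/(0.10/0.90) = 1.53.

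| p0 | f = 2% | f = 5% | f = 10% |
|---|---|---|---|
| 10% | RR 1.18, OR 1.20 | RR 1.45, OR 1.53 | RR 1.90, OR 2.11 |
| 9.26% | RR 1.20, OR 1.22 | RR 1.49, OR 1.57 | RR 1.98, OR 2.20 |
| 5% | RR 1.38, OR 1.41 | RR 1.95, OR 2.05 | RR 2.90, OR 3.22 |

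**Overlap that alone yields RR = 2.** Setting p1 = 2 × p0 gives f = p0/(1 − p0):

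- p0 = 10%: 0.10/0.90 = 11.1%, about 53 of 480 doses
- p0 = 9.26%: 10.2%, about 49 doses
- p0 = 5%: 5.3%, about 25 doses

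**False rejection.** A simple two-sided test at 0.05 of 480 against 5520 doses, ignoring clustering, rejects the true null about 84% of the time at p0 = 10% and f = 5%. At f = 2% the figure is 27% for p0 = 9.26% and 45% for p0 = 5%.

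**Effect of recoding.** Take p0 = 10% and 24 overlap doses. If these count only as MAEs, exposed doses have 0.10 × 456 = 45.6 errors in 456 (10.0%). Unexposed doses have 552 + 24 = 576 errors in 5544 (10.39%). RR = 10.0/10.39 = 0.96, a small bias the other way. If the 24 doses are excluded, the rates are 45.6/456 and 552/5520, both 10%, and RR = 1.

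**The case against.** Four objections deserve weight.

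- **The wording is one example in one of six rows.** Coding uses separate observation forms for workarounds and for errors (Multimedia Appendices 2 and 3), which are not shown and may contain a rule against double counting. This stands in part: how rows were actually coded cannot be known from the article, and the absence of such a rule from an article is no finding. But the example is the only content given for that category, and it contradicts Table 3 and the article's own definition.
- **The definitions may not overlap in practice.** A reader might infer from "operationalized as deviations from the available protocols" and "or from standard hospital policy and procedures" that every workaround is an MAE and the whole association is circular. The documents do not support that. The second phrase belongs to a definition taken from a cited source, the article then scores doses against prescriptions, and no Table 3 type is a pure scanning or procedure deviation. This overlap in wording is secondary.
- **The size is assumed.** This stands. The overlap share has no source in the documents, and at 2% the distortion is modest. The simple test also ignores the nurse and patient levels and collapses the four exposure categories to yes or no.
- **A repair can overreach.** This also stands. Limiting workarounds to identification, scanning and alerts would drop the other-procedure and work-related workarounds that the article includes, and would change the research question.

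**Conclusion.** The point holds for the nurse-related row of Table 2. Its examples are error outcomes placed in the exposure classification, and as written one event can enter the primary model as both exposed and a case. The direction of the resulting bias is clear: upward.

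Its size cannot be derived from the documents. With 8% of 6000 doses exposed, a 10% MAE rate without a workaround and a true relative risk of 1, an overlap of 5% of workaround doses gives 1.45 and about 11% gives the planned 2. These unclustered figures show that a modest overlap could matter. They do not show that it occurred, or that an observed association would be mostly an artefact.

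**What to change.** 1. Remove the two error outcomes from the nurse-related row of Table 2. Count a workaround only where a departure from the ward procedure, including other-procedure and work-related departures, can be coded without reference to whether the dose given matched the prescription.
2. State that for the primary outcome a procedure deviation alone is not an MAE: only Table 3 types, scored against the prescription, count.
3. Recode the affected rows and run, or rerun, the primary model. Enrollment is complete and analysis is under way, so declare this as a change made after data collection.
4. Add a sensitivity analysis that excludes events meeting both definitions, because scoring them only as MAEs makes them unexposed cases and pulls the estimate slightly toward or below 1. Exclude only doses where the same event supplies both codes. A dose with a separate workaround followed by an error must stay in, since that is the association under study.

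The cost is some recoding, a declared post hoc change and a slightly lower workaround count. No new observations are needed.

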### Sample Size Calculation

Prior studies [14,44-46] on the effect of BCMA show a substantial reduction (about 30%) of errors after the implementation of BCMA (from 14.4%, or 4743 errors in 32,972 observations, to 9.9%, or 2651 errors in 26,892 observations). The error rate of about 10% is a mix of all resulting errors, including those caused by workarounds. The purpose of our sample size calculation is to estimate the number of observations needed to reject the null hypothesis with a power of 90%. We performed a pilot study in 4 Dutch hospitals that were partially using BCMA (these hospitals did not participate in our final research) and found MAE rates, including time window errors caused by nurses and based on workarounds, fluctuating from 2% to 20% (2%, 4%, 5%, and 20%). We assume in our sample size calculation that 8% of medication administrations per patient per nurse result in a workaround. We also assume that the MAE rate associated with a workaround is 2-fold compared with the situation without a workaround; that gives us a relative risk of 2. With alpha of .05 and a power of 0.9, we need to observe 1500 individual medication administrations to patients per hospital to reject the null hypothesis.

### Data Monitoring

We will enter all data into an Access database (version 2010, Microsoft Corporation). The basis for the Access database will be the case report forms in Multimedia Appendix 1,Multimedia Appendix 2, and Multimedia Appendix 3. The first (Multimedia Appendix 1) is designed to collect data on potential risk factors for workarounds, the second (Multimedia Appendix 2) is designed to collect data on MAEs, and the third (Multimedia Appendix 3) is designed to collect data on observations of workarounds. These data will be made available to other researchers and editors on request. Data entry errors will be minimized by using multiple choice options and fixed data fields. At the end of the study, 10% of the entered data will be checked by a second researcher. If data entry errors are found, additional portions of 10% of the data will be checked until no errors are found within a portion. Also, a periodic backup of the study database of each hospital will be made and checked for missing data. Access to the research databases will be secured by passwords. Changing the format of the study documentation or study databases will be restricted to the primary investigator. New versions will be distributed from the central study location (the University of Groningen, the Netherlands). Before data analysis, we will lock the final database.

### Statistical Analysis

Data will be analyzed using IBM SPSS Statistics version 22 (IBM Corporation). We will analyze the potential association between workarounds and the occurrence of MAEs using univariate multilevel logistic regression, with the proportion of medication administrations with 1 or more errors as the dependent variable and the occurrence of workarounds as the independent variable. The nurse and the patient will be the levels in the multilevel analysis. We will analyze the occurrence of workarounds as a categorical variable, with the following categories: no workarounds (reference category), 1 workaround, 2 workarounds, and 3 or more workarounds. We will adjust for potential confounders by using multivariate multilevel logistic regression. The parameters in the multivariate multilevel logistic regression model will be hospital, ward type, day of the week, time schedule of medication administration rounds, ATC code, the number of drugs per patient per round, and the route of administration. We will report the adjusted odds ratio and 95% confidence interval. For the frequency and type of workarounds and MAEs, we will use descriptive statistics. Univariate and multivariate logistic regression will determine the association of the risk factors with the workarounds.

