**Methods:**

This is a multicenter prospective study on internal medicine and surgical wards of 4 Dutch hospitals using BCMA systems to administer medication. We will include a total of 6000 individual drug administrations using direct observation to collect data.

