### Setting

All included hospitals have implemented CPOE [10] and BCMA systems. They use a variety of software packages, both for the CPOE and for the BCMA systems. As a consequence, procedures for prescribing and medication administration differ between hospitals. Table 1 summarizes the main characteristics. Medication administration procedures within a hospital vary slightly between wards because of differences in patient groups or tasks (eg, in some hospitals, short stay surgical patients do not wear wristbands, but these are attached to the medication cart).

The included hospitals use bar code-labeled unit dose systems to distribute medication to inpatients. In the pharmacy departments, pharmacy technicians dispense bar coded medication for individual patients into trays labeled with the patient’s name and bar code. Trays are placed in medication carts in which they are then delivered to the wards once a day (or more frequently). Wards do not have ward-based medication stock (except for emergency medication). One of the selected hospitals uses so-called bedside assortment picking carts [29]. A cart contains all the medication commonly used on the ward. With this system, nurses select the medication for administration during the medication administration rounds.

In general, there are 4 scheduled medication administration rounds in the participating hospitals: 6-10 AM, 10-2 PM, 6-8 PM, and 8-10 PM. Medications are administered by 1 nurse. Nurse trainees are supervised by registered nurses. In the participating hospitals, there are approximately 10-20 inpatients admitted on a ward served by a registered nurse and a nurse trainee. A large ward is split into smaller units each serving 10-20 inpatients, each aided by a registered nurse and a nurse trainee.

During a drug administration round, nurses select the prescribed medication for each inpatient from the prefilled trays or from the bedside assortment picking carts. In addition to the cart, nurses also take along the computer on wheels or the workstation on wheels to access the CPOE system during the drug administration round.

Inpatients do not use their own (out-of-hospital prescribed) drugs.

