### Outcome Measures

The primary outcome measure of the study is the proportion of medication administrations with 1 or more MAEs. For this outcome, we will study the association between the MAE and the occurrence of 1 or more workarounds.

The secondary outcomes are the frequency and type of workarounds, the frequency and type of MAEs in the BCMA process, and the association of potential risk factors with workarounds.

**Table 1 table1:** Characteristics of the medication administration systems in the participating hospitals.

Item	Hospital 1	Hospital 2	Hospital 3	Hospital 4
Software system	RH Dharma	ViPharma	Klinicom	Pharma
System screen layout	Fixed layout	Fixed layout	Fixed layout	User-controlled screen layout
Administration system	Bedside assortment picking cart	Cart with prefilled patient-labeled trays	Cart with prefilled patient-labeled trays	Cart with prefilled patient-labeled trays
Log-in procedure for nurse	Once; automatic log-out after 15 minutes of inactivity	Once for 1 session	Once for 1 session	Once for 1 session
Log-out procedure for nurse	Manual; automatic log-out after 15 minutes of inactivity	Manual	Manual	Manual
Built-in additional check by nurse’s colleagues	Extra log-in for another nurse built in	Not possible	Extra log-in for another nurse built in	Not described in the instructions
Signal/alert system	Scanner beep and scanner warning light	Computer beep	Computer beep	Computer beep
Patient has no bar code	Not described in the instructions	Manual patient selection	Manual patient selection	Manual patient selection
Patient selection per administration round	Once, by selection of patient; automatically deselected after all medication for that round is administered	Twice, by selection and active deselection of patient after medication administration	Once, by selection of patient; automatic deselection after all medication for that round is administered	Once, by selection of patient; automatic deselection after all medication for that round is administered
Medication in the cart has no bar code	Robot-packed bar coded medication ordered from pharmacy	Manual drug selection	Manual drug selection	Nurse can overrule the system using her or his access code and manually select drug

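### With only nurse and patient as levels, the primary model omits the patient-round, so the standard error of the workaround effect is likely to be moderately understated if patients are seen in several rounds and workarounds and errors cluster there.

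*Protocol article*

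**What the plan says.** The protocol article (Statistical Analysis) analyses single drug administrations by multilevel logistic regression, with an error as the outcome and the number of workarounds in four categories as the exposure. On clustering it says: "The nurse and the patient will be the levels in the multilevel analysis". Rounds enter the adjusted model only as covariates, namely "time schedule of medication administration rounds" and "the number of drugs per patient per round". The Abstract gives the size: "We will include a total of 6000 individual drug administrations".

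Other sections describe how the data arise:

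- **Rounds.** Setting lists four scheduled rounds a day ("6-10 AM, 10-2 PM, 6-8 PM, and 8-10 PM") on units of 10 to 20 inpatients.
- **Sampling.** Data Collection requires "a minimum of 3 rounds every day and a weekly minimum of 18 rounds", and within these "the observer will observe as many different nurses as possible".
- **Patient selection.** Table 1 (Outcome Measures) has a row on selecting the patient in each round. For Hospitals 3 and 4 the entry is "Once, by selection of patient; automatic deselection after all medication for that round is administered". Hospital 1 is equivalent. Hospital 2 selects the patient and then actively deselects.

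**The concern.** A random patient intercept describes what a patient's administrations share over the whole period of observation. A random nurse intercept does the same for a nurse. Neither describes what is special to one patient in one round. If the wristband is not scanned in that round, every drug given then can carry the same workaround. If the round is late or the patient is missed, every drug can carry the same error.

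When exposure and residual outcome variation are both shared within a cluster that the model leaves out, the model counts more independent information on the exposure than there is. The quantity affected is the adjusted odds ratio for workarounds with its 95% confidence interval, which is the study's main result. An interval that is too narrow lets a true null be rejected too often.

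**Working it through.** **Step 1: does the plan describe a patient-round cluster?**

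- *Exposure.* The patient is selected once per round in three of the four hospitals. Table 2 lists a patient-related workaround (bed or loose wristband scanned instead of the patient) and a procedure-related one (nothing scanned). Either can cover all drugs of one round for one patient.
- *Outcome.* Table 3 counts as errors a drug given 60 minutes or more off schedule and a prescribed drug not given. A late round or a forgotten, absent or sleeping patient can produce these for all drugs at once.
- *Repeat rounds.* At least 3 rounds observed a day out of 4 scheduled, on units of 10 to 20 inpatients, make it likely that an inpatient is seen more than once. The number is not stated.
- *Covariates.* Time of round and number of drugs shift the mean for a type of round. They do not make two drugs in the same patient-round conditionally independent.

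**Step 2: the plan's own figure.** The plan gives no figure for clustering. Its only size figure is 1500 administrations per hospital (4 × 1500 = 6000). With 8% exposed, relative risk 2 and an overall error rate of 10% (the protocol's background rate), p0 = 0.10 / (0.92 + 0.08 × 2) = 0.0926 and p1 = 0.185. Treating administrations as independent, with power 0.90, the comparison of two proportions needs 1538 one-sided or 1850 two-sided. The one-sided result lies within 3% of 1500. The protocol states neither the sidedness nor the error rate that it used, and nothing here turns on the sample size. The check only shows that 10% and 8% are reasonable inputs for Step 3.

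**Step 3: simulation with no workaround effect.** For administration *i*,

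logit P(error) = α + u(nurse) + u(patient) + u(patient-round).

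From the protocol: 10% errors (α set to give this), 8% workarounds and about 1500 administrations per dataset. Assumed: 4 drugs per patient-round, nurse and patient SD 0.5, patient-round SD 0, 1.0 or 1.5, and 1, 2 or 4 rounds per patient. In the clustered settings 80% of patient-rounds share one workaround status. Each setting has 500 datasets, fitted by pseudo-likelihood with workaround as a yes/no term. Nurse and patient are crossed in both models shown.

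The ratio is the mean model standard error divided by the true SD of the log odds ratio; 1.00 is correct.

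| Rounds per patient | Patient-round SD | Workarounds | Nurse + patient: ratio, type I error | Patient-round added: ratio, type I error |
|---|---|---|---|---|
| 4 | 0 | clustered | 0.346/0.345 = 1.00, 3.8% | 1.01, 3.6% |
| 4 | 1.0 | clustered | 0.356/0.390 = 0.91, 5.4% | 0.99, 4.2% |
| 4 | 1.5 | clustered | 0.365/0.444 = 0.82, 8.0% | 0.95, 3.2% |
| 2 | 1.5 | clustered | 0.86, 8.2% | 0.98, 4.0% |
| 4 | 1.5 | vary by drug | 0.342/0.373 = 0.92, 4.8% | 0.95, 4.6% |
| 1 | 1.5 | clustered | 0.398/0.393 = 1.01, 2.6% | 1.01, 2.6% |

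Monte Carlo error is about 1 point on the type I error, √(0.05 × 0.95 / 500) = 0.0097, and about 3% on the ratio.

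Ratios of 0.91 and 0.82 mean standard errors 9% and 18% too small. A correct interval on the log scale would be 1/0.91 = 1.10 to 1/0.82 = 1.22 times as wide.

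**Step 4: crossed or nested.** The protocol does not say how nurse and patient are arranged. If patient is fitted within nurse, a nurse-by-patient effect nearly coincides with the patient-round when nurses change between rounds. In the settings with repeat rounds, clustered workarounds and patient-round variance, the ratios are then 0.93 to 0.98 and type I error 4.0% to 5.0%.

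**The case against.** The strongest reply is that the effect depends on three things the documents do not quantify: repeat rounds per patient, residual variance between patient-rounds, and workarounds that hold for a whole round. Without either of the first two the ratio returns to 1.00 or 1.01. Without the third the type I error is 4.8%, and most of the remaining shortfall in the ratio persists even with the added level. At a patient-round SD of 1.0 the type I error of 5.4% cannot be told from nominal. All of this stands.

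A reader might infer that the exposure is constant within a patient-round and that the interval is therefore certain to be too narrow. The documents do not support that. Table 2 also lists drug-specific workarounds, such as medication without a bar code and half tablets scanned as whole ones, and Table 1 sets several procedures drug by drug.

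A reader might also infer a larger error. A model with a patient intercept only, no nurse variance and exposure fixed for the whole patient-round gives standard errors 15% to 32% too small and type I error of about 9% to 16%. That is not the planned model, which has a nurse level too, so those figures do not describe this plan.

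It is fair to add that an article may leave the crossed or nested arrangement to a fuller plan, so its absence is not an error. What remains is that the article fixes the list of levels, the patient-round is not among them, and its own tables point to clustering there.

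**Conclusion.** The point holds conditionally. If patients are observed in two or more rounds and both workarounds and residual errors cluster by patient-round, the planned model is likely to understate the standard error of the workaround effect. With nurse and patient crossed, 4 rounds per patient, patient-round SD 1.0 to 1.5 and 80% of patient-rounds sharing one workaround status, the understatement is about 9% to 18% and the type I error about 5% to 8%. With 2 rounds per patient and SD 1.5 it is 14%, with type I error 8.2%.

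The variances, rounds per patient, drugs per round and sharing proportion are assumptions. The simulations used one hospital's share of the data, a yes/no exposure and no covariates. The direction is well supported by the design; the size is indicative and moderate.

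**What to change.** State in the analysis plan that nurse and patient are crossed random intercepts, and add a random intercept for patient-by-round, defined by patient, day and round. Data Collection already ties the computer output to these three identifiers, so no new data are needed. If the model does not converge, report cluster-robust standard errors as a sensitivity analysis. They should be clustered on a unit that contains whole patient-rounds, such as the patient. Report the estimated patient-round variance and the number of rounds per patient, so that readers can see whether the level mattered.

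The cost is longer fitting, possible non-convergence and somewhat wider intervals. The odds ratio also becomes conditional on the patient-round, so it can differ from the nurse-and-patient odds ratio when there is an effect, and the text should say so. If there is no patient-round variance, precision hardly changes (ratios 1.00 and 1.01 above).

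The added level addresses precision only. Where one event in the round, such as an absent patient, causes both the workaround and the error, that is confounding. A random intercept does not by itself remove it, and the interpretation should acknowledge this.
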